### Stage 5: From Technological Development to Pilot Implementation

After stage 4, we continue to engage with key stakeholders until we reach a saturation level whereby the model’s development either deeply reflects the complexity of localized needs and preferences in the concept design, making the technology more suitable for deployment and integration, or is deemed unfeasible.

Doing this will require repeated prototype engagement and daily discussion sessions with HCPs using the system. This session will be conducted specifically with our first focus group, including patients and carers, VCSE representatives, GPs, community nurses, social workers, domiciliary carers, pharmacists, and acute health of older people teams. Each session will include an introduction explaining the purpose of improving the tool and meeting clinical needs, a brief demonstration, an opportunity to test and use the prototype in small groups, and then report on their experiences. The group of 15 participants will then be subdivided into 5 groups of 3 (20%) participants each and asked to complete the following tasks: use the device to generate a summary based on a prerecorded pseudoanonymized patient-clinician interaction, review its associated AI-generated summary, edit it, and integrate it into an electronic patient record. After completing these tasks, prototype engagement participants will return to the larger focus group to share their experiences, challenges, and suggestions. Topics will likely include ease of use and intuitiveness, clarity and relevance of the summaries, to what extent they could imagine the technology fitting within existing workflows, responsiveness of the tool to correction and feedback, consistency and acceptability of the terminology, and recommendations for enhancements. This process will be repeated at least twice but primarily until saturation is reached, which is defined as broad HCP satisfaction with the usability of the devices.

After saturation, if stakeholder support for these model implementations exists, the research team will then work closely with the second focus group from stage 2, which includes local information governance specialists, IT services, data specialists, managers (hospital, primary care network, and care homes), local authorities, integrated care boards, and regional NHS regulatory boards (n=15). Across 3 sessions, this group will aim to create bespoke implementation strategies to reflect the 2 PCN systems’ infrastructure limitations, support teams’ specific needs embedding the models into daily practice, and deliberate methods of providing an ongoing support system for later pilot-testing and wider-scale deployment. In session 1, the group outlines a strategy to implement our system into their existing workflows and IT systems and identifies necessary adjustments to enable the model’s integration. Session 2 will ensure that the previous strategy meets regulatory and ethical guidelines, and finally, session 3 outlines a package of technical support and seeks to achieve agreement on responsibilities and channels for accessing this support channel and who provides the training.

After ensuring that both adopters and key stakeholder implementers are happy with the technology and that it could be implemented into their health systems, we will reach out to each clinical team engaged in its implementation, alongside local PCN technology deployment and support specialists, to finalize an agreed upon implementation and evaluation timeline and ensure they are happy with our proposed evaluation objectives and metrics (see stage 6 described subsequently). Once approved, we will engage each team and deliver essential training on using the system. This training will include preparing the microphone, recording, creating the PCC summary, sharing the summary in the electronic patient record, and building on past summaries with new clinical encounters for the same patient. Once all teams are happy with setting up, creating, sharing summaries, and accessing support, final verification of resources, allocation training, and support will be conducted, and then the AI system will go live.

### Stage 6: Evaluation of Implementation

#### Overview

The final part of this study will evaluate the implementation of the AI summarization model within a health care setting. This evaluation will explore whether the summarizations positively impact HCPs and patients. To do this, we will analyze the impact on clinical workflows, patient outcomes, and perceptions of the impact on perceived workload; assess the usability and acceptability; and determine whether any biases or medicolegal risks emerge and if the system positively impacts personalized and meaningful patient-clinician interactions and relationships.

#### Time-Motion

This evaluation will first address the impact on clinician workflows. The process will include a time-motion study with 9 HCPs based across primary care clinic (n=3, 33%), intermediate care (n=3, 33%), and domiciliary care (n=3, 33%). We will observe HCPs in their respective work settings under 2 conditions for each participant. First, we observe HCP-patient interaction and their documentation process with standard non-AI methods. Second, we observe HCP using the AI PCC summarization system.

To do this, the research team breaks down the process into stages, one measuring normal practice workflow. In normal practice, stages include (1) reviewing previous records before engagement; (2) engaging in HCP-patient interaction; (3) documenting the consultation in the electronic patient record postencounter; and (4) HCP submitting, sending, or embedding the summary into the electronic patient record. Our AI system includes the following stages: (1) reviewing AI PCC summary before a patient engagement; (2) setting up the recording device; (3) engaging in the HCP-patient interaction; (4) packing away the device; (5) HCPs checking the summary for acceptability; and (6) HCP submitting, sending, or embedding the summary into the electronic patient record. We will then analyze the data to identify (1) whether the implementation of our system reduces the time taken and (2) if there are further opportunities to streamline and better embed the technology into a care pathway [41,42].

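### The time-motion stage list for the AI condition has no stage for creating or editing the summary, leftover notes or record review, so the time saving may be overstated

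*Protocol article*

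**What the plan says.** Protocol article, Stage 6, Time-Motion, plans a "time-motion study with 9 HCPs based across primary care clinic", intermediate care and domiciliary care, three in each setting, observed "under 2 conditions for each participant". The conditions are introduced in this order: "First, we observe HCP-patient interaction and their documentation process with standard non-AI methods", then "Second, we observe HCP using the AI PCC summarization system".

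Each condition has its own stage list. Usual practice has four stages. The first is "1) reviewing previous records before engagement", the third is "documenting the consultation in the electronic patient record postencounter", and the others are the encounter and submission to the record. The AI condition has six: reading the AI summary beforehand, device set-up, the encounter, packing away, and finally "HCPs checking the summary for acceptability; and (6) HCP submitting, sending, or embedding the summary into the electronic patient record".

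Stage 5 describes what users do with the tool. In the prototype sessions they generate a summary from a recorded interaction and then "review its associated AI-generated summary, edit it, and integrate it into an electronic patient record". The training before go-live also covers creating the summary.

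The first question put to the time-motion data is whether the system reduces time. The Results section expects these data to be the evidence of potential time saved against usual documentation.

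**The concern.** The two lists are not like for like. The two usual-practice stages most open to a saving, record review and note-writing, are absent from the AI list. What replaces them is reading the AI summary and checking it. Work that the protocol itself expects of AI users, namely creating and editing the summary, has no stage. Nor do any notes the clinician still writes, or any look at the ordinary record.

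An observer who times only the listed stages would record this work in one condition and miss it in the other, and the missed minutes would appear as time saved. Saving HCP time is one of the project's stated aims. This is its only observed time measure, since the interviews and the usability scale capture perceptions. Minutes not recorded on the day cannot be recovered in the analysis.

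**Working it through.** The plan states no sample-size basis, expected saving or duration for this component, so there is no figure to reproduce. The check is a comparison of the two lists, followed by the bias that any difference implies.

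**Step 1: activities side by side** (Stage 6, Time-Motion, set against other sections)

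| Activity | Usual-practice list | AI list | Is it expected in the AI condition? |
|---|---|---|---|
| Review of earlier records | Yes | No (AI summary only) | Inferred: the model summarises recorded encounters; drawing on existing record data appears only under Future Directions |
| Reading the AI summary | Not applicable | Yes | Yes |
| Device set-up and packing away | Not applicable | Yes | Yes |
| Encounter | Yes | Yes | Yes |
| Creating the summary | Not applicable | No | Yes: Stage 5 prototype task and training |
| Checking the summary | Not applicable | Yes | Yes |
| Editing the summary | Not applicable | No | Yes: Stage 5 names review and editing as separate tasks |
| Writing notes | Yes | No | Inferred: Limitations foresees a separate application or only partial integration |
| Submission | Yes | Yes | Yes |

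Two stages, the encounter and submission, are common to both lists. Four activities have no AI stage. Two of these (creating, editing) are user tasks in the protocol's own text. The other two (remaining notes, record review) are plausible inferences.

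**Step 2: the bias**

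Let T_N and T_A be the true minutes per encounter in usual practice and with AI, and U_N and U_A the minutes left untimed in each.

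- Measured saving = (T_N − U_N) − (T_A − U_A)
- True saving = T_N − T_A
- Measured minus true = U_A − U_N

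Here U_A = creating + editing + remaining notes + record review, counting only what is not timed. U_N is any usual-practice work that escapes timing. It need not be zero, because the Background says that some community staff enter notes at the end of the day.

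**Step 3: size**

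The documents give no minutes. As an assumption, take U_A between 0 and 5 minutes per encounter:

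- U_A = 0, U_N = 0: overstatement = 0 − 0 = 0 minutes.
- U_A = 5, U_N = 0: overstatement = 5 − 0 = 5 minutes. A tool that saves nothing would appear to save 5.
- U_A = U_N: overstatement = 0, whatever the common value.

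The first case holds if creation and corrections are timed inside listed stages and the summary fully replaces both the note and the record review.

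**Step 4: order**

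If all 9 HCPs are observed under usual practice first, order and condition coincide for every participant and no analysis can separate them. The sign is unknown. Getting used to being observed would favour the AI condition, and unfamiliarity with a new tool would count against it.

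**The case against.** The strongest reply is that the lists need not be exhaustive. HCPs are observed directly, and an observer who runs the clock from packing away to submission would capture any editing. Checking a summary for acceptability can naturally include correcting it. The summary is meant to cover clinical issues as well as preferences (Stage 4), so it may replace the note. This is a small component of a feasibility study, and Stage 5 still has the evaluation metrics to be agreed with the clinical teams. These points stand: they make the bias conditional. They do not remove the mismatch, because Stage 5 names review and editing separately and nothing in the time-motion text says that the interval between stages is timed.

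It may also be said that the AI list is not one-sided, since it charges the tool with set-up and packing away. That is true, but those minutes are real work correctly counted, so they do not offset minutes that go unrecorded.

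A reader might infer from the order of the two conditions that the sequence itself adds to the saving. The text does not support this. The wording may only enumerate the conditions, session scheduling may be left to a fuller protocol, and an order effect has no fixed direction.

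**Conclusion.** The AI stage list omits two tasks that the protocol elsewhere gives to users, creating and editing the summary. It also has no place for remaining notes or review of the ordinary record. If only the listed stages are timed, the saving is overstated by U_A − U_N minutes per encounter, which is 0 to 5 minutes under the assumed range with nothing untimed in usual practice.

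A reader might go further and conclude that a saving is built into the design, or put a percentage on it. The documents support neither. The bias can be zero, and with no minutes given any percentage would only restate its own assumptions. The part about creating and editing rests on the protocol's text. The part about notes and record review rests on inference. If usual practice is always observed first, order is confounded with condition in an unknown direction.

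**What to change.** Use one stage list in both conditions, entering zero where a stage does not occur:

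1. review of any record or summary before the encounter;
2. device set-up;
3. the encounter;
4. packing away;
5. creating or waiting for the summary;
6. checking and editing;
7. any other notes for that encounter, including those written later the same day;
8. submission.

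Compare total time across all stages, and use the stage times to look for ways to streamline.

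State the order of observation. If usual practice always comes first, report that order and condition cannot be separated and that the direction is unknown. Alternating AI and usual sessions after go-live is an option, but a trade-off: AI summaries already in the record could then be read in the usual-practice sessions and contaminate that condition.

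The cost is a longer observation sheet and follow-up of same-day notes, with the same 9 HCPs. The change must be made before observation starts; the Stage 5 step at which metrics are agreed with the teams is a natural point for it.

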#### Acceptability and Usability

To evaluate the model’s usability and acceptability, we also apply a longitudinal mixed method approach involving semistructured interviews (n=15) and the System Usability Scale (SUS; n=20). Participants include HCPs (eg, general practitioners, community nurses, social workers, and domiciliary carers). Longitudinal interview and questionnaire assessments will occur at 3 time points: baseline, 1 month after intervention, and 6 months after intervention.

Semistructured interviews will be conducted face-to-face or via videoconferencing platforms (n=15) to receive feedback from HCPs to help understand their perceptions of whether the model has streamlined the documentation, perceived workload, and ease of use; how effectively the model adheres to ethical, privacy, and information governance standards; and any challenges encountered and suggestions for improvement. Importantly, as interpretability and explainability are now a mandatory regulatory requirement in various regulatory contexts, such as the European Union, participants will discuss their comprehension of the rationale behind AI-generated recommendations, clarity and interpretability of outputs, and ability to identify potential inaccuracies or biases. This identification of challenges will be documented, and the model adapted accordingly [43].

Immediately after the interview, participants will complete the SUS, a validated 10-item questionnaire that measures perceived usability. Responses are scored between 0 to 100. Higher scores indicate better usability [44-46]. Finally, this process will be repeated in our longitudinal assessments at 3 time points: baseline, 1 month after intervention, and 6 months after intervention. Together, these provide a helpful insight into the model’s usefulness as it becomes more deeply embedded into day-to-day practices.

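### The SUS is planned for 20 HCPs but tied to an interview held with 15, and its first round, at baseline, is not comparable with the rounds after go-live

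*Protocol article*

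**What the plan says.** The point lies in one subsection of the protocol article, Acceptability and Usability (Methods, Stage 6).

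- **Numbers.** The approach combines "semistructured interviews (n=15) and the System Usability Scale (SUS; n=20"). The interview number is given a second time: "Semistructured interviews will be conducted face-to-face or via videoconferencing platforms (n=15").
- **Respondents.** "Participants include HCPs (eg, general practitioners, community nurses, social workers, and domiciliary carers"). No group that completes only the SUS is described.
- **Administration.** "Immediately after the interview, participants will complete the SUS". No other route is given.
- **Schedule.** "Longitudinal interview and questionnaire assessments will occur at 3 time points: baseline, 1 month after intervention, and 6 months after intervention". After describing the interview and the SUS, the subsection adds that "this process will be repeated in our longitudinal assessments at 3 time points: baseline, 1 month after intervention, and 6 months after intervention".
- **Content.** The SUS is "a validated 10-item questionnaire that measures perceived usability", scored 0 to 100. The interview asks HCPs for "their perceptions of whether the model has streamlined the documentation, perceived workload, and ease of use", among other topics.

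Stage 5 supplies the context for baseline. Each clinical team is trained to record encounters and to create and share summaries, and the system goes live after that. Earlier in Stage 5, a mixed group of 15 (patients, carers, voluntary-sector representatives and HCPs) tries a prototype.

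**The concern.** Two features of the procedure do not fit together.

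First, a form handed out at the end of an interview reaches only those interviewed. With 15 interviewees, the stated 20 SUS respondents are not obtained by the stated route.

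Second, the same interview and questionnaire are run at baseline. If baseline precedes go-live, HCPs are asked to rate the usability of a system they have not used in practice, and to say whether it has already streamlined their documentation. The stated purpose of the repeated measurement is to see how useful the model is as it beds into daily work. A series whose first value rests on anticipation or a training session, and whose later values rest on live use, does not serve that purpose if it is read from baseline. A fall from baseline could mean disappointed hopes, and a rise could mean initial wariness; neither would show that usability had changed.

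**Working it through.** **Step 1. Reproduce the stated SUS number.** Inputs, all from Acceptability and Usability: 15 interviews, SUS n = 20, 3 time points, SUS completed directly after the interview.

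- One form per interview gives SUS n = 15, so the stated 20 is not reproduced.
- Gap: 20 − 15 = 5 HCPs per time point; 5/20 = 25%.
- Forms planned: 20 × 3 = 60. Forms delivered by the stated route: 15 × 3 = 45. Shortfall: 15 of 60.

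**Step 2. Could other Stage 6 interviews close the gap?** The subsection Impact on PCC plans interviews with 10 HCPs. With an overlap of k people between the two sets, the number of distinct interviewees is 15 + 10 − k, which runs from 25 (k = 0) to 15 (k = 10). It equals 20 only if k = 5. The article states no such overlap and attaches neither a SUS nor time points to those 10 interviews. They do not explain the 20.

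**Step 3. What the shortfall does to precision.** The 95% half-width for a mean is t(0.975, n − 1) × SD/√n.

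- n = 15: 2.145/√15 = 0.554 SD.
- n = 20: 2.093/√20 = 0.468 SD.

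The article gives no SUS standard deviation. Over an assumed range of 15 to 20 points:

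| Assumed SD | Half-width, n = 15 | Half-width, n = 20 | Difference |
|---|---|---|---|
| 15 | 8.3 | 7.0 | 1.3 |
| 20 | 11.1 | 9.4 | 1.7 |

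The loss is small on a 0 to 100 scale, and the article sets no precision target against which to judge it.

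**Step 4. Where baseline falls.** The schedule contrasts baseline with two points described as after the intervention. Stage 5 places go-live after training and a final verification. On the natural reading, no HCP has used the live system at baseline; what they may have had is training and, for any who sat in the mixed prototype group, a trial of the prototype. The article does not say that the Stage 6 respondents come from that group.

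**Step 5. What each round rates.**

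| Round | Experience behind the rating | Can the interview ask about effects already felt? |
|---|---|---|
| Baseline | Expectation, or training at most | No |
| 1 month | Live use | Yes |
| 6 months | Live use | Yes |

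Only the last two rounds measure the same thing. If the AI-system SUS is confined to them, the count is 20 × 2 = 40 forms with a stand-alone form, or 15 × 2 = 30 if the SUS stays tied to the interview.

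**The case against.** The strongest reply on the count is that 15 and 20 stand side by side in one sentence, and the usual mixed-methods reading is a survey of 20 people of whom 15 are interviewed. The sentence on timing may apply to interviewees only, and a condensed article can leave the other five to the full protocol. This is a plausible intention, so a reader who infers that the SUS cannot be collected goes too far: 15 forms per round are collectable as described, and nothing bars a separate form for the rest. What stands is that the only procedure the article gives does not produce its own number.

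The strongest reply on baseline is that the term is undefined and that Stage 5 training includes hands-on work with recording and summaries. A post-training SUS could be a legitimate first-use rating, so the documents do not show that a baseline score is expectation and nothing else. Nor is the whole baseline interview unanswerable: topics such as privacy, governance and workload can be discussed beforehand, and a semistructured guide can be adapted. What stands is that the article neither defines the baseline rating nor separates it from the later ones, and that it says the same process is repeated at all three points.

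Finally, no change-from-baseline analysis is specified. The Results section says only that SUS scores and qualitative data will identify the degree of usability and acceptability, and the 1- and 6-month scores are already scheduled. This limits the severity. It does not remove the need to say which rounds are comparable.

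**Conclusion.** The point holds in two parts. The stated procedure gives 15 SUS forms per time point against a planned 20: a shortfall of 25%, or 45 of 60 forms overall. Separately, the baseline rating is not comparable with the 1- and 6-month ratings. The first part rests on the article's text alone. The second assumes that baseline precedes go-live, which is the natural but unstated reading.

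A reader might combine the two and conclude that only 30 of 60 forms, or half, are of use. The documents do not support that: it treats the five unassigned HCPs as certainly lost and any rating after training as worthless, and the article establishes neither.

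Severity is modest. The SUS is a descriptive secondary measure with no stated test, power or precision target, and the precision lost at n = 15 is about 1.3 to 1.7 points under the assumed standard deviations. The change is still worth making, because it settles what the longitudinal usability result can be taken to mean.

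**What to change.** 1. **Reconcile the numbers.** State that all 20 HCPs complete the SUS as a stand-alone form at each scheduled round, the 15 interviewees doing so after the interview; or restate the SUS number as 15.
2. **Settle the first rating.** Either start the SUS for the AI system at 1 month, or define the first rating as post-training, label it so in every report, and do not use it as the reference for change.
3. **Base change in usability on 1 to 6 months.**
4. **Limit the baseline interview** to current practice and expectations, and hold questions about effects already experienced for the later rounds.

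Scoring the existing record system with the SUS at baseline is an optional addition. It would measure a different system and is not part of the required change.

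The cost is a few sentences. The stand-alone option adds no forms beyond the 20 per round already planned, though 5 HCPs per round would complete theirs outside an interview. The downside is that no pre-use reference score is reported for the AI system. The article says that, as of August 2025, the study has neither funding nor ethical approval, so the wording can be changed before any data are collected.
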